### Losses to follow-up

Women may temporarily move, or they may permanently move from a tabanca, in which case we may have difficulty tracking their child survival outcomes. We will try to learn outcomes from neighbours and friends but we will not attempt to personally interview women who have moved outside their enumeration cluster. When an eligible woman cannot be found, we will include the information from relatives, neighbours and other sources in the cluster about her pregnancy and survival outcomes, and her children's survival outcomes, for the primary analysis. If a fieldworker did not meet with a woman in a prior monitoring, but they do meet with her on a subsequent visit, the field worker will ask the woman to verify the previously reported data that was received from relatives, neighbours or other sources.

### Consent

This trial will employ three levels of consent:

• At the state level, approval of the protocol will be sought from the Ministry of Health in Guinea-Bissau.

• At the Tabanca level, field supervisors will arrange meetings with local leaders to seek consent. In all tabancas in the trial, consent will be obtained from the leaders in the following manner. The local leaders will be informed about the protocol for the trial in their local language. They will then be asked to inform and seek consent, as appropriate for their ethnic group and specific traditions, from the members of their community. Consent will be given in oral form during this community meeting with written documentation of the discussions for verification. This process of obtaining consent from the 'guardians' of the clusters is common in trials in which the intervention is delivered at the level of a cluster and it is not possible to ask for prior consent for randomisation from individuals within the cluster [11].

• Given this process, women who are asked to take part in the quarterly enumeration and who consent to complete this enumeration are considered to have given their implied consent to participate in the trial. Women not living in the tabancas at that point, or who are not present, who subsequently fill the eligibility criteria will be informed about the study.

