### Women eligible for analysis within clusters

The analysis of the trial will be based on outcomes for eligible women, and children living with them, and on the outcomes from new pregnancies arising during the trial.

A woman is eligible for inclusion in the analysis of the trial if:

 • She lives in one of the 146 selected clusters.

 • She is a resident in one of the households mapped and is interviewed during the baseline survey.

 • She gives consent to participate in the trial.

 • She reports that she is between 12 and 49 years of age or/and she reports that she is the primary caregiver for a child under five years of age at the time of the baseline survey.

 • The tabanca she lives in gives consent to participate in the trial.

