### Exclusion criteria for women and children

Women and their children will be excluded from the analysis if they do not satisfy all inclusion criteria.

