### Data collection and surveillance

#### Initial baseline survey

The initial baseline survey will be conducted before randomisation. The information from this survey will be used to define clusters and generate lists of eligible women and children. The survey will record birth and child survival histories for each eligible woman.

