#### Quarterly monitoring survey

In both arms of the trial in each cluster data will be collected by the field research team on a quarterly basis. Every eligible woman included in the trial will be interviewed, and child survival histories will be updated. The quarterly monitoring will permit measurement of the primary endpoint of the trial on an ongoing basis. Survey teams will visit all 146 clusters approximately every three months. They will visit each cluster for at least one full day, and they will make multiple attempts during the day to meet women and their children enrolled in the trial. During this enumeration they will update child survival outcomes for each woman, and they will record whether the woman is pregnant. If a woman is pregnant they will record how many months she is pregnant. If the field worker is unable to find the woman, they will ask the same questions to someone living in the same household, or a neighbour, and record the information reported by that person on child survival outcomes and pregnancy for the missing woman. If they are unable to find a woman during three successive quarterly visits, they will enquire about the specific reasons for absence, and a supervisor will follow-up and attempt to find the woman and record data based on the responses. If it is not possible to find a woman after nine months, then her records will be recorded as missing from that point on, or until she can verify her history through a direct interview.

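### Consent, a condition for entering the primary analysis, is taken from the quarterly enumeration after randomisation, so women interviewed at baseline can be filtered out once their arm is known

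*Protocol article*

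**What the plan says.** All references are to the protocol article.

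- Women eligible for analysis within clusters lists, among the criteria that must be met, "She gives consent to participate in the trial". The same list requires residence in a mapped household and an interview in the baseline survey.
- Exclusion criteria for women and children: "Women and their children will be excluded from the analysis if they do not satisfy all inclusion criteria".
- Consent, third level, names the act that counts as the individual woman's consent. Women approached for the quarterly enumeration "who consent to complete this enumeration are considered to have given their implied consent to participate in the trial".
- Initial baseline survey: "The initial baseline survey will be conducted before randomisation".
- Quarterly monitoring survey: "In both arms of the trial in each cluster data will be collected by the field research team on a quarterly basis".
- Losses to follow-up, on eligible women who cannot be found: "we will include the information from relatives, neighbours and other sources in the cluster about her pregnancy and survival outcomes". These reports are used in the primary analysis.
- Consent, on women living elsewhere or absent at that point: those "who subsequently fill the eligibility criteria will be informed about the study".

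**The concern.** In a cluster trial whose intervention cannot be hidden, membership of the primary analysis should not depend on anything a participant does after she can see her arm. Here one inclusion criterion does. Intervention villages receive health clubs, medicines, outreach and delivery kits. Control villages receive strengthened emergency facilities and the surveys. Willingness to keep answering surveys could differ between the two, and a refusal takes out the woman's children as well.

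The protocol guards against this kind of bias elsewhere. It keeps households enumerated after randomisation out of the primary analysis, and it leaves out children fostered after randomisation. Consent is the route that stays open. A refuser removed as ineligible would also not appear as a loss to follow-up, so an imbalance between arms could go unseen.

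**Working it through.** No figure in the protocol tests this point. The first part compares sections. The second is an illustration with assumed inputs.

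**1. The sections side by side**

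1. Consent is required for analysis, and failing any criterion excludes the woman and her children (the two eligibility sections).
2. The only individual act named as consent is agreeing to the quarterly enumeration (Consent).
3. The baseline survey precedes randomisation and is described separately. The quarterly survey is described by trial arm, so it follows randomisation.
4. The arm is evident by then: only intervention villages have the second enumeration and mother's cards (Methods of enumerating women in intervention arm after randomisation) and the health clubs and medicines package (Table 1). The word unblinded does not appear; this is an inference, but a safe one.
5. The article records no individual consent at baseline and has no rule that keeps a woman who refuses the quarterly survey in the analysis.
6. A woman never met at a quarterly visit has performed no act of consent, so by steps 1 and 2 she is out. Losses to follow-up and Quarterly monitoring survey bring in her outcomes by proxy, but the former does so for eligible women. Whether she belongs to the primary set is therefore not settled.

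**2. How large could the effect of refusal be?**

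Inputs: true relative risk 0.70 (the 30% reduction in Sample size calculation) and control risk 9% (same section). Assumed, because the document gives neither: the share refusing in each arm, r_c (control) and r_i (intervention), and the excess risk h in refusing families.

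If an arm has risk p and refusers have risk h·p, the women left have risk p(1 − r·h)/(1 − r). The observed relative risk is the true one times

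F = [(1 − r_i·h)/(1 − r_i)] / [(1 − r_c·h)/(1 − r_c)].

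- r_c = 0.08, r_i = 0.03, h = 1.5: F = (0.955/0.97)/(0.88/0.92) = 0.9845/0.9565 = 1.029. Control appears as 9% × 0.9565 = 8.61%, intervention as 6.3% × 0.9845 = 6.20%, relative risk 0.72.
- r_c = 0.10, r_i = 0.02, h = 2: F = (0.96/0.98)/(0.80/0.90) = 0.9796/0.8889 = 1.102, relative risk 0.77.

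If the excess risk is instead measured against consenting families (ratio R), the factor is G = [1 + r_c(R − 1)]/[1 + r_i(R − 1)]: 1.04/1.015 = 1.025 and 1.10/1.02 = 1.078.

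| Refusal, control | Refusal, intervention | h or R | F | 0.70 appears as | G | 0.70 appears as |
|---|---|---|---|---|---|---|
| 8% | 3% | 1.5 | 1.029 | 0.72 | 1.025 | 0.72 |
| 10% | 2% | 2 | 1.102 | 0.77 | 1.078 | 0.755 |
| 5% | 5% | 2 | 1.000 | 0.70 | 1.000 | 0.70 |
| 3% | 8% | 1.5 | 0.972 | 0.68 | 0.976 | 0.68 |
| 2% | 10% | 2 | 0.907 | 0.64 | 0.927 | 0.65 |

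The last two rows swap the arms (F and G become their reciprocals). The direction also reverses if refusing families have lower mortality than the rest.

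**The case against.** The strongest reply is that the primary set is largely fixed before allocation. A woman must have been interviewed at baseline, children already born before the survey must have been recorded by name in it, later-enumerated households are kept out, and intention-to-treat is defined by village of residence at baseline. A reader might infer that the analysis set is recruited after allocation. The documents do not support that: nobody can be added, and only removal is possible.

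A reader might also infer that unmet women are simply dropped. The proxy rules point the other way, and records are set to missing only from nine months onward. What stands is a conflict between those rules and the Consent section, not a rule that drops these women. A third tempting reading is that absent women may join the analysis later. The sentence only promises to inform them, and the baseline-interview criterion still applies.

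Both arms receive the same survey, from a research team separate from service delivery and after community consent. Nothing documents differential refusal, and the illustration rests wholly on assumed rates. All of this stands, and it limits the point to active refusal plus an unresolved status for unmet women.

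The reference to the quarterly enumeration may be a slip for the baseline survey. If so, the text still needs correcting, because as written it helps define the primary set. Nor is this a detail left to the full analysis plan, since the article itself states both the eligibility rule and the act of consent.

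Finally, calling a refusal at the first quarterly visit a loss to follow-up does not recover the outcomes. That is right: the missingness remains, and the gain is that it becomes visible.

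**Conclusion.** The point holds in a limited form. As written, the protocol places one filter on its primary analysis set after allocation, through refusal of the quarterly survey, and it leaves open whether women never met but reported by proxy are included.

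The bias is possible, not demonstrated. A reader might conclude that intention-to-treat is broken or that the result will be biased. The documents do not support this, because they give no refusal rate and no risk among refusers. Under assumed refusal of 8–10% in control and 2–3% in intervention, with 1.5 to 2 times the risk, a true relative risk of 0.70 would appear as about 0.72 to 0.77. Equal refusal with equal excess risk leaves it at 0.70, and the opposite imbalance would exaggerate the benefit. The correction is still worth making, because it concerns the primary population of a mortality trial and requires only wording.

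**What to change.** - Define the primary analysis set before allocation: all women interviewed at baseline in consenting villages, their children listed at baseline, and their later live births as already specified.
- In Consent, tie the individual woman's consent to the baseline interview, not to the quarterly enumeration.
- State that women not met at quarterly visits remain in the set, with outcomes from the proxy sources in Losses to follow-up.
- Count a later refusal as loss to follow-up from its date, keep the data up to that date, and report refusals by arm.
- Keep the commitment to inform absent women, and add that those not interviewed at baseline do not enter the primary analysis, in line with the eligibility criteria and the rule on late-enumerated households.

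The cost is wording and a slightly higher reported loss rate. Refusals will still cause missing data, but visibly and by arm.

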### Sample size calculation

The sample size has been calculated to give 80% statistical power to show a 30% reduction in the proportion of death before the age of five in the intervention clusters compared to the control clusters.

We assume that the average size of the population in eligible households for each cluster will be 350 people defined by the algorithm described earlier. We also assume an average annual number of live births of twelve per cluster (the crude birth rate is estimated to be 35 per 1000 population in the region according to discussion with regional health authorities). Thus, we expect to observe approximately 48 children under five per cluster at the time of randomisation (taking into account the estimated probability of death at birth and consequent time intervals below 5 years of age based on a baseline survey conducted in Guinea-Bissau in preparation for this trial) and a further 30 births during the following two and a half years.

We used an intraclass correlation coefficient (ICC) of 0.02 to allow for clustering. This was estimated from the DHS survey in India, using ten years data from Maharashtra state. There are no similar DHS data for Guinea-Bissau. In a Nepalese trial examining neonatal mortality, the ICC was estimated to be 0.00644, but since there were generally only one or two births per woman, and the clusters in that trial were much larger, we believe the ICC here will be higher.

Under the above assumptions, the expected proportion of children who will die before the age of five during a two and a half year period in the control arm is 9%. Assuming 10% loss to follow up in both control and intervention arms, 130 clusters in total will be needed to show a 30% reduction in the proportion of deaths before the age of five in the intervention clusters compared to the control clusters with 80% statistical power and with 2-sided significance level of 5%. We are planning to map and randomise all the 146 clusters, defined as eligible during the baseline survey, to allow for possible dilution of the impact of the intervention that might be caused by migration.

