## Background

### Research justification and relevant literature

Guinea-Bissau is a small country in West Africa with a population of 1.7 million. The country is very poor with GDP per capita at $352 per person. The WHO and UNICEF report that under-five child mortality is 203 per 1000 in 2004, ranking the 10^th ^highest amongst 192 countries [1].

A prospective survey conducted during 2003–2005 estimated that under-five child mortality is 308 per 1000 in rural regions of Guinea-Bissau, with neonatal mortality of approximately 70 per 1000 [Rodriguez, A., Tome, C: Seguimento e avaliacao de indicadores do plano nacional de desenvolvimento sanitario e do projecto multisectorial de luta contra sida. Bandim Health Project, 2006]. Our baseline survey in the region where this study is to be implemented found an under-five child mortality rate of 154 per 1000 as reported by women aged 12 to 49 for their 2002 to 2007 pregnancy history. While both estimates suggest very high child mortality, the difference in these estimates may reflect methodologies (prospective versus retrospective monitoring of births and deaths) and differing regional coverage. There is very little information on the causes of child deaths. The Bellagio Child Survival Study Group concluded that neonatal deaths in low income countries were mostly due to sepsis acquired around and soon after birth, birth asphyxiation, and congenital abnormalities. They estimated that diarrhoea, pneumonia and malaria cause more than three quarters of child deaths after the neonatal period [2]. The Joint United Nations Programme on HIV/AIDS estimates a relatively low 1.8% HIV prevalence in Guinea-Bissau in 2007 compared to other Sub-Saharan African countries where the overall prevalence estimate is around 6% [3].

The high child mortality in rural Guinea-Bissau is likely to be due to multiple factors. Although most of the diseases that cause child deaths are probably preventable, low income and logistics have limited the quality and availability of public healthcare. Even if clinical services were improved, poor health knowledge and education and limited number of trained health personnel, probably contribute to poor treatment seeking practices and preventable child deaths. Poor roads and remoteness also make it difficult for guardians to seek care for their children.

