### Interventions

Table 1 outlines the activities that each arm of the project receives during the first two and one half years.

**Table 1 T1:** Trial activities by arms of the trial in the first 2.5 years

Activities	
Intervention (73 clusters)	Control (73 clusters)

Hospitals for caesarean sections and clinics for emergency care are buttressed	Hospitals for caesarean sections and clinics for emergency care are buttressed: materials from the programme are available to controls if needed for emergencies and staff trained in IMCI as needed.
Health clubs organized and participants receive:	
2 years of training in health issues.	
Training and mentoring for several village health workers, who are members of the health clubs, in issues related to maternal and child health.	
Maternal and child health outreach programme operated by 6–8 trained mentor nurses.	
Free institutional deliveries for high risk mothers and delivery kits to all pregnant mothers.	
Medicines package for children.	
Quarterly monitoring surveys	Quarterly monitoring surveys

At the start of the intervention, health clubs will be organised in each community. The number of health clubs will be chosen so that there are approximately 60 households per club. These clubs will meet regularly for two years and cover topics related to maternal and child health that are expected to impact on child mortality:

 • Recognition, treatment and prevention of malaria, pneumonia and diarrhoea

 • Safe pregnancy and delivery

 • Care for newborns

 • Hygiene and sanitation

In addition to health clubs, communities will meet at the start of the interventions to select village health workers. These village health workers will be members of the health clubs, and will work closely with health clubs. The village health workers will be given intensive block training (3–5 days for each session) by registered nurses, "nurse trainers", in the following areas:

 • Recognition, treatment and prevention of diarrhoea

 • Recognition, treatment and prevention of malaria

 • Recognition, treatment and prevention of pneumonia

 • Safe pregnancy and delivery

 • Care for the newborn

 • Nutrition and child growth monitoring

The training for these workers will reflect the Ministry of Health's policies and IMCI recommendations [10].

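### The 9% control-arm death proportion does not follow from the baseline survey's 154 per 1000, which gives about 5.9%; at that value the stated 80% power is not reached

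*Protocol article*

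**What the plan says.** In the protocol article, the section on sample size calculation aims for "80% statistical power to show a 30% reduction in the proportion of death before the age of five in the intervention clusters" relative to control. It assumes 12 live births per cluster per year, about 48 children under five per cluster at randomisation and 30 further births over two and a half years. The survival probabilities behind the 48 are said to be "based on a baseline survey conducted in Guinea-Bissau in preparation for this trial". The ICC is 0.02 and loss to follow-up is 10% in both arms.

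From these assumptions the section concludes that the expected proportion of deaths "during a two and a half year period in the control arm is 9"%, and that "130 clusters in total will be needed to show a 30% reduction" "with 80% statistical power and with 2-sided significance level of 5"%. All 146 eligible clusters are randomised; the 16 above 130 are kept for dilution of the effect through migration. No derivation of the 9% is given.

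The Background (research justification and relevant literature) reports that the trial's own baseline survey "found an under-five child mortality rate of 154 per 1000 as reported by women aged 12 to 49", covering pregnancies from 2002 to 2007. It also cites 203 per 1000 nationally and 308 per 1000 from a prospective survey of rural regions. The abbreviations list defines the under-five mortality rate as under-five deaths per 1000 live births in a year.

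**The concern.** The 9% is tied to a named source, and the result of that source is printed elsewhere in the same article. The birth rate, number of children and length of follow-up are also printed, so the expected proportion can be computed directly, and it comes out at about two thirds of the stated figure.

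The control-arm proportion is the main driver of power here, because the effect is set as a relative reduction: fewer control deaths mean a smaller absolute difference to detect. If 9% is too high, the 80% power claim fails, and the reserve of 16 clusters is spent on restoring power rather than on covering migration. A null result could then be read as coming from a trial with assured 80% power when it had somewhat less.

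**Working it through.** **Inputs** (all from the protocol article). Sample size section: 12 births per cluster-year, 48 + 30 = 78 children, 2.5 years, 30% reduction, two-sided 5%, ICC 0.02, 10% loss, 130 clusters required, 146 randomised. Background: 154, 203 and 308 per 1000.

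**1. The plan's own figure.** Children analysed per cluster: m = 78 × 0.9 = 70.2. Design effect: 1 + (70.2 − 1) × 0.02 = 2.384. For 9% against 6.3%:

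n per arm before clustering = (1.960 + 0.842)² × (0.09 × 0.91 + 0.063 × 0.937) / 0.027² ≈ 1,517

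Total clusters = 2 × 1,517 × 2.384 / 70.2 ≈ 103

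So 130 is not reproduced. Other standard two-sided 80% formulas built on 78 children give about 93 to 122. At 9% and m = 70.2, 130 clusters would give 88% power and 146 about 92%. The plan's 130 therefore contains an unstated conservative step. This does not affect the results in step 3, which use the full 70.2 children per cluster.

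**2. The control-arm proportion.** With steady births and mortality, under-five deaths per year equal births per year times under-five mortality, whatever the age pattern of death. So

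proportion = 12 × 2.5 × mortality / 78 = 30 × mortality / 78

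| Under-five mortality per 1000 | Deaths per cluster | Proportion |
|---|---|---|
| 154 (trial's baseline survey) | 4.62 | 5.9% |
| 203 (national) | 6.09 | 7.8% |
| 234 (needed for 9%) | 7.02 | 9.0% |
| 308 (other rural survey) | 9.24 | 11.8% |

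The 234 is 0.09 × 78 / 30. It appears nowhere in the article, and none of the three cited rates gives 9%.

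**3. Power at 5.9%.** Let p0 = 0.0592 and p1 = 0.7 × 0.0592 = 0.0415; the difference is 0.01777. With K clusters in total, the effective number per arm is (K/2) × 70.2 / 2.384, and

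power = Φ( (p0 − p1) / √[(p0(1 − p0) + p1(1 − p1)) / effective n] − 1.96 )

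- The variance sum p0(1 − p0) + p1(1 − p1) is 0.0955.
- K = 130: effective n = 1,914, standard error 0.00706, z = 2.516, power 71%.
- K = 146: effective n = 2,150, standard error 0.00666, z = 2.666, power 76%.
- About 161 to 162 clusters would give 80%.
- With 146 clusters, the reduction detectable at 80% power is about 31.4% rather than 30%.
- With no loss to follow-up at all (m = 78), power is 73% and 78%.

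**4. Sensitivity with 146 clusters.**

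| Mortality per 1000 | ICC | Power |
|---|---|---|
| 154 | 0.02 | 76% |
| 154 | 0.015 | 82% |
| 154 | 0.00644 | 93% |
| 203 | 0.02 | 87% |
| 308 | 0.02 | 97% |

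Power of 80% is reached at about 170 per 1000 with ICC 0.02, or at an ICC just under 0.017 with 154 per 1000.

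**The case against.** The strongest reply is that 9% rests on an undisclosed input and is not a proven slip. Five points support it.

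- **Under-reporting.** The 154 comes from retrospective reports, whereas the trial counts deaths prospectively each quarter. The Background itself says that method and regional coverage may explain the gap between estimates. The 9% lies between the values implied by 203 and 308, so it could be a deliberate upward adjustment. This is plausible, but the sample size section mentions no adjustment and names the baseline survey.
- **Meaning of 154.** Many children born in 2002 to 2007 had not reached age five. If 154 were a raw proportion dead, full under-five mortality would be higher. The article does not say how it was calculated.
- **Link between the sections.** The survey is cited in explaining the 48 children, not directly beside the 9%. That the two sections mean the same survey is an inference. It is a strong one, since the article describes only one baseline survey for this trial.
- **The 48 children.** A reader might take the 48 as separate proof of error, because 60 births in five years at 154 per 1000 leave at least 60 × 0.846 = 50.8 alive. The documents do not support that. The 48 could reflect population growth, or a higher mortality schedule that would also fit 9%.
- **ICC.** Holding the ICC at 0.02 while the proportion falls implies more relative variation between clusters. With k the between-cluster coefficient of variation, ICC = k²p/(1 − p). At 9% an ICC of 0.02 means k = 0.45. Keeping k = 0.45 at 5.9% gives an ICC of 0.0127 and power of 81% with 130 clusters and 85% with 146. This stands as a reason to call the shortfall conditional. The plan, however, fixes 0.02 and argues against the lower Nepalese value.

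What remains is that the printed inputs and the printed 9% do not agree, and the article offers nothing to reconcile them.

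**Conclusion.** The point holds in a limited form. On the article's own birth rate, child count and baseline-survey mortality, the control-arm proportion is about 5.9%, not 9%. At 5.9% and the plan's ICC, 130 clusters do not give 80% power, and the 16 kept for dilution do not restore it even before any dilution. The shortfall with the 146 clusters actually randomised is small: 4 percentage points of power, or a detectable reduction of 31.4% instead of 30%.

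This rests on steady births and mortality, on the two sections meaning the same survey, on 154 being a full under-five rate as the article defines it, and on ICC 0.02.

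A reader might go further and conclude that the trial is badly underpowered. The documents do not support that: power with 146 clusters is 87% at 203 per 1000 and 97% at 308. Nor can a larger loss be inferred by calibrating to the sponsor's 130, since the method behind that number is unknown. A reader might also infer from the support given to control clusters (Interventions, Table 1) that control mortality will fall below the survey rate. The article does not quantify that effect, and it carries no weight here.

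**What to change.** In the sample size section, do one of two things:

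- replace 9% by the proportion that follows from the baseline survey (about 5.9% at 154 per 1000); or
- state the under-five mortality behind 9% (about 234 per 1000), justify it, for example by an explicit adjustment for retrospective under-reporting, and reconcile it with the 154 in the Background.

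Then restate the power for the 146 clusters, with its range over 154, 203 and 308 per 1000 and over the ICC. The birth histories recorded at baseline could inform both the control proportion and the ICC.

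The cost is a revised paragraph and a short table. Clusters, design and analysis stay as they are. If the survey figure is adopted, the stated power becomes somewhat less favourable.

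### The 130 clusters stated for 80% power do not follow from the 48 children plus 30 births per cluster that the analysis counts; they match the 48 alone

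*Protocol article*

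**What the plan says.** The protocol article, section Sample size calculation, gives these planning inputs:

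- **Target:** "The sample size has been calculated to give 80% statistical power to show a 30% reduction", with a two-sided 5% significance level.
- **Control proportion:** "the expected proportion of children who will die before the age of five during a two and a half year period in the control arm", put at 9%. A 30% relative reduction makes the intervention proportion 6.3%.
- **Clustering:** "We used an intraclass correlation coefficient (ICC) of 0.02 to allow for clustering".
- **Children per cluster:** "we expect to observe approximately 48 children under five per cluster at the time of randomisation", then "and a further 30 births during the following two and a half years".
- **Loss to follow-up:** 10% in each arm.

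The result is that "130 clusters in total will be needed to show a 30% reduction in the proportion of deaths before the age of five". All 146 eligible clusters are nevertheless to be randomised, and the excess over 130 is explained as cover for dilution of the effect by migration.

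The section Children eligible for analysis admits children living with an eligible woman at randomisation. It also admits live births to eligible women after randomisation. Both groups therefore enter the primary analysis.

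**The concern.** The paragraph prints a nearly complete set of inputs and a result, so a reader can redo the sum. Counting the children that the paragraph lists and the eligibility rules admit (48 + 30 = 78 per cluster), the sum does not give 130.

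Two things depend on the figure. The first is the power claim: if 130 is not the number for 80% power, the reader does not know what power the trial has. The second is the reserve. The 146 clusters are presented as 130 plus a margin of 16 for dilution, and that margin is only as reliable as the 130. A further question follows: if the calculation used only some of the eligible children, does the 9% describe those children or all of them?

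**Working it through.** **Inputs** (all from Sample size calculation): p0 = 0.09; p1 = 0.7 × 0.09 = 0.063; difference d = 0.027; z values 1.96 and 0.8416; ICC = 0.02; 48 children plus 30 births per cluster; 10% loss. Allocation is 1:1 (73 and 73 clusters, Table 1).

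**Step 1: children per arm before clustering.**

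- Unpooled: (1.96 + 0.8416)² × (0.09 × 0.91 + 0.063 × 0.937) / 0.027² = 1,517.
- Pooled variance under the null: 1,521.
- Pooled with continuity correction: 1,594.

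**Step 2: clusters per arm.** With m children per cluster, clusters per arm = n × [1 + (m − 1) × 0.02] / m, rounded up, then doubled for the total.

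**Step 3: a route that reproduces 130.** Take only the children present at randomisation, less loss: m = 48 × 0.9 = 43.2.

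- Design effect = 1 + 42.2 × 0.02 = 1.844.
- 1,521 × 1.844 / 43.2 = 64.92, so 65 per arm and **130 in total**.
- The unpooled 1,517 gives 64.77, also 130.

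**Step 4: the same calculation with all 78 children.**

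| How the 10% loss enters | Design effect | Total, no continuity correction | Total, with correction |
|---|---|---|---|
| Inside the cluster size, m = 78 × 0.9 = 70.2 | 1 + 69.2 × 0.02 = 2.384 | 1,521 × 2.384 / 70.2 = 51.65 per arm: 104 | 54.13 per arm: 110 |
| Design effect at 78, then division by 0.9 | 1 + 77 × 0.02 = 2.54 | 54.90 (unpooled) or 55.03 (pooled) per arm: 110 or 112 | 57.67 per arm: 116 |

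A log-relative-risk version gives 106 and 112 for the two rows. The formula based on the between-cluster coefficient of variation (k = 0.45) gives 98 at m = 70.2, further from 130. Charging the loss twice, which is not standard, gives at most 122.

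**Step 5: power with all 78 children** (m = 70.2, pooled form). The effective number per arm is clusters × 70.2 / 2.384.

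| Total clusters | Effective children per arm | Power |
|---|---|---|
| 104 | 52 × 70.2 / 2.384 = 1,531 | 80.3% |
| 130 | 65 × 70.2 / 2.384 = 1,914 | 88.2% |
| 146 | 73 × 70.2 / 2.384 = 2,150 | 91.5% |

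**Step 6: the reserve.** As stated it is 146 − 130 = 16 clusters. With all 78 children it is 146 − 116 = 30 to 146 − 104 = 42.

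**Step 7: unequal cluster sizes.** The design effect becomes 1 + [(CV² + 1) × m − 1] × 0.02. At m = 70.2 without continuity correction, a CV of 0.6 gives 126 clusters and a CV of 0.7 gives 134. A CV between these would therefore also lead to about 130. The section states no such allowance.

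**The case against.** The strongest defence is that 130 is not arbitrary. It follows exactly from figures in the paragraph if the cluster size is the 48 children at randomisation less 10% loss, with every other input unchanged. Leaving out births, whose exposure is shorter, might have been a deliberate caution. The article also never states 78 as the cluster size used, and a condensed article commonly leaves the formula to the full protocol. This stands as far as it goes, and it rules out two stronger readings.

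- A reader might infer that no use of the stated inputs gives 130, so that a different ICC or control proportion must lie behind it. With all 78 children at m = 70.2, an ICC of about 0.029 or a control proportion of about 7.3% would indeed be needed. Step 3 shows that neither is required, and the article gives no sign that either was used.
- A reader might infer that the trial is too small. The discrepancy runs the other way: on the article's own assumptions 130 clusters exceed 80% power, and 146 are randomised in any case.

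The defence does not remove the mismatch. The paragraph lists the 30 births among the children to be observed and then derives its result from the assumptions above it. A calculation on 48 children drops 30 of 78, or 38%, of the children who will be analysed, and nothing in the text says so.

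The unequal-size explanation is possible but unsupported. The section on defining clusters aimed at 40 to 52 households each, which makes a CV of 0.6 to 0.7 less plausible, although clusters with fewer households were allowed.

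**Conclusion.** The stated requirement of 130 clusters for 80% power does not match the design as written. With the 48 children and 30 births that the analysis admits, the requirement is about 104 to 112 clusters, or up to 116 with a continuity correction. The stated figure is thus 12% (130/116) to 25% (130/104) above it. Power is about 88% at 130 clusters and about 91% at 146.

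These figures assume equal cluster sizes and take the article's ICC of 0.02, 9% control proportion and 10% loss as given; whether those inputs are right is a separate matter. The exact match with 48 children less 10% makes omission of the births the likelier explanation. The article does not show whether that, an unequal-size allowance or something else produced 130.

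The error is conservative and puts neither the number of clusters nor the trial's conclusion at risk. What it leaves wrong is the stated power and the stated margin for dilution.

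**What to change.** Revise the last paragraph of Sample size calculation to:

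1. State the number of children per cluster used, where the 10% loss enters and any allowance for unequal cluster sizes.
2. Reconcile 130 with the 48 + 30 children analysed. If the births were left out deliberately, say so and why.
3. Confirm that the 9% refers to the same children as the cluster size.
4. Restate the clusters needed for 80% power, the power of the 146 randomised and the resulting reserve for dilution by migration. The reserve is 16 clusters as written, and about 30 to 42 if all 78 children count.

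The cost is rewording one paragraph. The number of clusters, the randomisation and the data collection do not change.
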